Audit and feedback and continuous quality improvement: We will conduct monthly audit and feedback activities to track progress and promote continuous quality improvement using clinic-context data reports. Key emerging themes that impact delivery processes will be quickly fed back to the facility for possible actions. Best practices for demand creation, clinical PrEP provision, male partner engagement and HIV testing, clinic flow, and retention strategies will be discussed with and shared across clinics for possible adoption. Detailed clinic-level reports will be generated at baseline and 6-monthly to triangulate delivery processes including adherence to or adaptations to core components of PrEP delivery and impact on FP services.

Streamline clinic data, program data abstraction, and PrEP supply chain: Routine program data are riddled with incompleteness, which may affect effective evaluation of public health programs. During the pre-implementation, we will work with clinics and Kisumu Health leadership to get PrEP commodities (e.g., PrEP, HIV tests) to FP clinics, develop accountability and tracking systems. We will work with clinics and MOH/NASCOP to define and optimize simple sustainable data systems that can utilize clinic-level data and reports to improve services. This may include modification of current PrEP clinical encounter form as well as FP registers or electronic medical records (existing in a few clinics but generally not in FP clinics) to include indicators for STI counseling and treatment, PrEP use, and tracking. As part of the process to optimize data systems and quality improvement, program nurses will abstract some routine program data from (e.g., risk assessment tool or RAST, PrEP clinical encounter/PrEP registers, FP registers) to evaluate how effectively and efficiently integrated delivery of FP and comprehensive HIV services including PrEP services is disseminated and implemented. With the introduction of PrEP as part of routine HIV prevention services, indicators of current standard HIV prevention care, male partner testing, PrEP use (expected to be minimal) have been added to list of indicators to the Ministry of Health. We will work with clinics to promote reporting of HIV prevention service and PrEP indicators to the County and MOH/NASCOP information

systems. We will optimize the data systems with a dedicated data clerk embedded in each of the clinic starting in the pre-implementation period and transition to clinic staff after 12 months.

**Cross-sectional and Program exit surveys:** User experience is an important part of a successful program service delivery. Within the program we will use cross-sectional quantitative and exit surveys administered to random women at clinic to understand quality of care services and women's satisfaction with services. Exit surveys will be conducted within 3 months of program start and then 6 monthly by trained staff, as clients are exiting the facility. The cross-sectional quantitative surveys will help obtain important data that cannot be obtained from program tools (e.g., the FP register) including detailed demographics and HIV risk behavior characteristics of women accessing FP services. Exit surveys will inform program continuous quality improvement activities.

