## DESIGN AND PROCESS OF INTRODUCING PREP DELIVERY IN FP CLINICS

Systematic integrated screening for HIV risk and counseling for and provision of PrEP will be introduced and actively promoted in family planning clinics in Kisumu. These strategies will be introduced in staged three successive waves (steps), occurring every 3 months, with 4 clinics per step or stepped-wedge design (**Figure 2**). The order at which clinics initiate the implementation will be determined

[figure not shown]

by randomization stratified by clinic size, identified as likely to have a marked effect on implementation outcome. Randomization process will take place at a meeting with the Kisumu County Health leadership, implementing health facilities and led by the project staff. Prior to initiating implementation of the program, we will conduct clinic-wide training for health providers at each clinic and we will engage existing FP providers in continuous quality improvement to optimize delivery. At all implementing clinics, we will conduct a pre-implementation needs assessment and observation of current services to optimize data and PrEP supply systems. During this pre-implementation period, a minimum of 3 months for each clinic, we will assess and document current processes on HIV counseling and testing, male partner testing, PrEP counseling and use (expected to be minimal), STI counseling and treatment, male partner STI testing and treatment of women infected with STIs, incident HIV and STI. During implementation, we will optimize delivery of PrEP in combination HIV prevention using existing FP clinic staff supported through ongoing technical assistance from program technical team and MOH/NASCOP and Kisumu County Health supervision team to audit for process indicators of implementation progress and continuation quality improvement. On-the-job training of new staff will be promoted and we will conduct refresher CME-like training quarterly or as needed.

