**Sample size and power:** For this facility-level intervention, the co-primary outcomes will be: 1) proportion of women accessing FP services that are counseled and screened for HIV risk, and 2) proportion of women who initiate PrEP. HIV testing is the entry point for all HIV services. Although HIV counseling and testing an expected service in FP clinics, it is not routinely done in most FP settings. Assuming a conservative 50% rate in the current practice, with 3600 total women screened, we will have  $\geq 80\%$  power to detect a meaningful increase of 10% or more in proportion of new clients screened for HIV prevention. We assume the average proportion being screened at project start will be between 50% and 70%, accounting for heterogeneity in baseline levels and treatment effect, we will have  $\geq 80\%$  for the range of likely baseline levels of screening. We expect that prior to starting the intervention, PrEP initiation will be very low, averaging  $<2\%$  (ranging from 0-5% across clinics). After the intervention, we expect to see PrEP initiation among general population women increase to a mean of 22% (based on preliminary work, [name] et al *PLOS Med* 2019), much higher among women with risk factors for HIV. Sample size and power calculations for stepped wedge cluster randomized trials should account for possible heterogeneity in intervention effects so that the study is not underpowered. We expect that the overall increase of +20% will reflect a range of true intervention effects across clinics depending on clinic factors, likely distributed between 10%-30%. Accounting for heterogeneity in baseline levels and intervention effect, if each clinic offers universal counseling for HIV risk and offer of PrEP for at least 100 new women per step, totaling at least 4800 new women overall, using a two-sided  $\alpha=0.05$ , the study will have excellent power to detect the expected increase in PrEP initiation (**Table 2**). To fully understand how public health clinics build new efficient systems for delivery of integrated FP and HIV prevention services, we will abstract data on all HIV-uninfected women accessingservices in implementing clinics in order to establish the underlying denominator in the program. Based on data from the baseline preparatory periods (monthly volume of ~1000) and a conservative PrEP screening rate between 10-30%, we estimate that program data on up to 25000 women accessing services across the 12 FP clinics will be needed for thorough evaluation of this new program beyond the statistical sample size. This sample size will permit a full-scale test of the system, since the efficiency in delivery is in large part at the system level, above and beyond the individual client encounter.

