| Target of action | Health providers in FP clinics                                                                                              | Health providers in FP clinics                                                                                                        | Clinic manager/ Health providers in FP clinics                                    | FP clinics/clinic staff                                                                                       | FP clinic systems/Clinic managers                                                                 |
| Temporality      | 2-4 week prior to implementation                                                                                            | Baseline                                                                                                                              | Implementation                                                                    | Baseline                                                                                                      | Baseline                                                                                          |
| Frequency        | MOH PrEP curriculum delivered in 5 modules over 2 weeks at the facility premises. Ongoing refresher 3-6 months or as needed | Weekly TA visits for 6 months, then monthly for 6 months. 3 monthly with study nurse for 18 months then 3 monthly alone for 6 months. | 2 weekly for 3 months, then monthly for 9 months                                  | At baseline, 6, and 12 months                                                                                 | Baseline, then ongoing and fully optimized within 12 months.                                      |
| Outcomes         | # of providers trained, provider knowledge gain, confidence to deliver PrEP                                                 | Fidelity, Maintenance (sustainability)                                                                                                |                                                                                   | Adaptations to clinic flow. Client time in clinic, provider time spent to provide services. PrEP continuation | Data and M & E tools completeness PrEP commodity stock out                                        |

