*Training and capacity building for PrEP implementation:* Training health care providers is an essential component of integrating a new clinical strategy in public health settings. The program will work with MOH/NASCOP and Kisumu County Health Team to support clinics' readiness to deliver PrEP in a combination HIV prevention package in FP clinics. Training will be conducted at each of the participating clinics (in-facility training) using the approved case-based interactive Kenya MOH PrEP training curriculum^31; our team contributed to the development of this curriculum. Content specific to FP clinics will

be added, including topics on FP, STI, treatment and partner testing services with the goal of equipping providers with the comprehensive knowledge and skills to provide integrated FP and combination HIV prevention services including PrEP services. A standardized pre-and post-test about PrEP will be used to assess knowledge gain. The training will be conducted at each facility premises and curriculum modules will be delivered over a 2 weeks period immediately prior to implementation, and then CME-like quarterly refresher training during delivery. Clinics will begin PrEP delivery after the training. For each training, as part of quality improvement processes, we will administer a standardized pre- and post-test. All trainees will receive their pre- and post-test scores. We will also summarize de-identified scores of the trainees by cadre to be shared with MOH/NASCOP and Kisumu County Health Team, in order to generate discussions that will foster quality improvement processes.

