PrEP technical assistance and county supervision: We will conduct ongoing technical assistance to clinics using trained program nurses to coach, mentor, and guide FP clinics to troubleshoot emerging challenges with integrating new services. Technical advisors (TA) will be project nurses with training in PrEP delivery. Prior to implementation, Program nurses will undergo an intensive 2 weeks didactic and protocol training conducted by study investigators, in collaboration with Kenya MOH and Kisumu Health officials. TA will conduct structured periodic visits to each clinic to coach and mentor the health care providers and observe and document PrEP implementation processes with a specific focus on processes that are effective or not and aspects of delivery that are changing with time. Using rapid-cycle analysis approaches, TAs will make summary reports at the end of each clinic visit highlighting what changed, why it changed, who initiated the changes, and outcome of any changes instituted. Best practices will be shared across all clinics for possible adoption. For the first 3 months post-introduction, study nurses (TAs) will visit clinics weekly for 3 months, and then complete monthly visits through the 12-month intensive implementation phase. During year 2, TA activities will scale back to observe sustainment phase. Throughout the first 18 months, the TAs will be accompanied to facility visits by County health and or Kenya MOH/NASCOP supervisors to audit for process indicators for FP services, HIV prevention services, and PrEP and progress.

Novel clinic and patient flow mapping: We will conduct workflow mapping at all sites to identify potential bottlenecks, differences and commonalities among sites at baseline and 6 monthly. We will solicit provider engagement in defining new flow maps to accommodate new tasks and patient flows. Current and future flow maps will be created for each site to demonstrate new pathways.

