**Delivery and implementation outcomes:** Evaluation of implementation outcomes will be framed by the RE-AIM and CFIR (as detailed in the preceding paragraph) frameworks. The RE-AIM guides evaluation of the public health impact of complex interventions, capturing formative, process, and outcome dimensions on the individual, organizational, and policy levels and gives a multi-dimensional understanding of the core components that drive public health impact. Reach, will be defined as proportion and subgroups of women accessing FP services who are screened and take PrEP, Effectiveness, will be assessed at individual level as 1) PrEP adherence, quantified by tenofovir levels in dried blood spots, and 2) women staying HIV free; Adoption will be assessed as the proportion of 1) clinics approached which implement intervention 2) targeted providers who are trained and implement PrEP thereafter; fidelity to PrEP delivery will be assessed as proportion of core components delivered per protocol; and Maintenance, a measure sustainability over time, will be the number of clinics delivering PrEP at 6 and 12 months after the intensive technical assistance .

**Analysis for quantitative data:** For each outcome, we will compare outcome during periods of usual care vs.

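### Pre-crossover time is analysed as usual care although training and supply work fall within it and best-practice sharing has no step limit, which can dilute the screening effect.

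*Protocol*

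**What the plan says.** **Design.** Under *Design and process of introducing PrEP delivery in FP clinics*, the rollout is in "staged three successive waves (steps), occurring every 3 months, with 4 clinics per step". Each clinic has a pre-implementation period of at least 3 months, in which current practice is documented.

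**Analysis.** Under *Data, Analysis for quantitative data*, "we will compare outcome during periods of usual care vs" periods of intensive implementation, over baseline and steps 1-3. The exposure is the clinic's intervention status in the step in which the woman is enrolled. No weeks are set aside between the two conditions.

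**What is scheduled before crossover.**
- Training: under *Training and capacity building*, "curriculum modules will be delivered over a 2 weeks period immediately prior to implementation". The Temporality row of Table 3 says "2-4 week prior to implementation".
- Supply: under *Streamline clinic data, program data abstraction, and PrEP supply chain*, "During the pre-implementation, we will work with clinics and Kisumu Health leadership to get PrEP commodities (e.g., PrEP, HIV tests) to FP clinics".
- Readiness: under *Clinic readiness*, a clinic that scores low may receive a brief corrective intervention before it starts.
- Technical assistance: Table 3 times it at Baseline. The section on technical assistance counts the weekly visits from introduction.

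**Sharing between clinics.** The technical-assistance section says "Best practices will be shared across all clinics for possible adoption". The audit-and-feedback section repeats the idea and lists demand creation, PrEP provision, HIV testing and clinic flow among the topics. Neither limits sharing to clinics already implementing.

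**The concern.** In a stepped wedge the effect is estimated against clinic time before crossover. Training and supply are named components of the strategy under test. If women seen while these are already at work count as controls, the control level rises and the estimated effect shrinks.

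The screening co-primary is the exposed one. Counselling and risk screening need little more than instructed staff, so they can change as soon as training begins. Unrestricted sharing adds a second route: waves start 3 months apart, so lessons from wave 1 arise while waves 2 and 3 are still controls. A larger sample restores power but does not remove this bias.

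**Working it through.** **Inputs from the protocol.** 12 clinics, 3 waves of 4, 3-month steps (13 weeks), hence 4 periods. For screening: "Assuming a conservative 50% rate in the current practice, with 3600 total women screened", a 10-point increase, two-sided alpha 0.05, stated power 83.8% (Table 2). 3,600 women over 12 × 4 = 48 clinic-periods is 75 per clinic-period. No intraclass correlation or variance component is given.

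**1. Share of control time taken by training.** Control clinic-periods: 4×1 + 4×2 + 4×3 = 24, or 24 × 13 = 312 clinic-weeks.
- Of all control time: 12×2/312 = 7.7% to 12×4/312 = 15.4%.
- Of the last control period of each clinic: 2/13 = 15% to 4/13 = 31%. For wave 1 this is the only control period in the comparison.

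**2. Standard error behind the stated power.** SE = 0.10 / (z at 0.838 + 1.960) = 0.10 / 2.946 = 0.0339.

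**3. Power after attenuation.** If control time already receives a share c of the effect, power = Φ(0.10(1 − c)/0.0339 − 1.960).

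| Assumed c | Effect (points) | Power |
|---|---|---|
| 0 | 10.0 | 83.8% |
| 5% | 9.5 | 79.9% |
| 10% | 9.0 | 75.5% |
| 20% | 8.0 | 65.4% |
| 30% | 7.0 | 54.1% |

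Power reaches 80% at (0.842 + 1.960)/2.946 = 0.951 of the full effect, so at 4.9% attenuation.

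**4. Training weeks counted as control.** This needs a model: generalised least squares with fixed periods, a random clinic intercept (SD τ), a random intervention effect (SD η) and binomial variance at 75 women per clinic-period. Without variance components in the protocol, 83.8% cannot be reproduced from its inputs. Assuming τ = 0.10 and η = 0.049 gives 83.9%, 86.2% and 90.7% for the three 10-point rows of Table 2, against the stated 83.8%, 86.2% and 90.8%. That is a calibration, not a reproduction.

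In this model a leak confined to each clinic's last control period carries a weight of 1.14. If staff work at half the full effect during training (an assumption):
- 2 weeks: 1 − 1.14 × (2/13) × 0.5 = 0.91, so 9.1 points and 76.8% power.
- 4 weeks: 1 − 1.14 × (4/13) × 0.5 = 0.83, so 8.3 points and 68.2% power.

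Recalibrating η over τ from 0.02 to 0.20 gives 76.4-78.7% and 67.3-72.8%.

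**5. Relative risks.** Screening: 0.60/0.50 = 1.20; with a 20% leak, 0.60/0.52 = 1.15. PrEP initiation, expected to go from 2% to 22%: 0.22/0.02 = 11; if control uptake were 3%, 0.22/0.03 = 7.3.

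**6. PrEP-initiation power.** With 100 women per clinic-period and assumed τ = 0.02, η = 0.05, a 25% leak leaves 15 points and more than 99% power; a 50% leak leaves 10 points and 99.6%. The protocol's statement that "the study will have excellent power to detect the expected increase in PrEP initiation" is therefore not undermined on this ground.

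**The case against.** **PrEP initiation.** The training section says that PrEP delivery starts once training is done, and the design section expects little PrEP use before implementation. Stock in a clinic is not an initiation. A reader might infer that both co-primary effects are biased, but a leak into PrEP initiation is not shown. This point stands in full. All that remains is that the relative risk is sensitive to small changes in a low control rate.

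**Sharing.** No sentence says that waiting clinics receive best practices. The technical-assistance visits are counted from introduction, and Table 3 places audit and feedback under Implementation. A reader might infer that contamination is planned; the documents show only that nothing prevents it. The wording does cover every clinic, and whom to exclude is a matter of conduct that an analysis plan cannot repair afterwards.

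**Training and mapping.** Preparation just before go-live is normal in a stepped wedge and biases the estimate only if those weeks are analysed as control. An analysis plan that is not shown could set a transition. However, the protocol already assigns exposure by whole step. Baseline workflow mapping is largely observation, and no passage puts the revised flow into use early, so it is not counted here.

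**Size.** The leak shares are assumptions. HIV testing is already an expected family-planning service and baseline screening is put at 50-70%, so test kits on site are not clearly new. This stands: the calculations show sensitivity, not an expected bias.

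**Conclusion.** The point holds for the screening co-primary as a possible dilution towards zero. Pre-crossover time is labelled usual care, while training and supply work are scheduled within it, sharing has no step limit and no transition is stated. The document does not fix the size of the bias. What it does fix is a thin margin at 3,600 women: about 5% attenuation loses the 80% target. The 76.8% and 68.2% figures rest further on the assumed half effect and the calibrated variance components.

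For PrEP initiation, a smaller relative risk is possible but not demonstrated, and power is not at material risk. The stronger readings, that both effects are certainly biased or that waiting clinics will certainly be coached, go beyond the text.

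**What to change.** 1. State that, until step 3 starts and all clinics have crossed over, best practices are shared only among clinics that have crossed over. This costs no sample size.
2. Define the training and supply-preparation weeks immediately before go-live as a transition period of the same length in every clinic, excluded from the primary analysis. Keep it short: dropping the whole last pre-crossover quarter would leave only 45-54% power. HIV tests that are already part of usual care should not be withheld, since that would push the control condition below usual care.
3. Reconcile the start of technical assistance (Baseline in Table 3, after introduction in the text) and the timing of training (2-4 weeks before in Table 3, the 2 weeks immediately before in the text).

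**Cost.** About 8-15% of control clinic-time is lost. At 3,600 women, power for the 10-point screening effect becomes 81.8% (2 weeks) or 79.1% (4 weeks) in the calibrated model, with ranges of 81.6-82.2% and 78.8-80.2% over τ from 0.02 to 0.20. The planned volume offsets this: 3,600 women over 12 months is 300 a month, against the roughly 1,000 a month that the protocol cites.
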